### Outcome Measures

#### Overview

For all measures (Table 1), the time frame will be the current point-in-time at which the participant is answering the survey. It is important to note that the measures do not presently pertain to specific types of disabilities, thereby potentially limiting our ability to relate the findings to participants with disabilities. Still, the measures and subsequent findings can be used to inform future studies engaging survivors of domestic violence, generally, and serve as a base for the inclusion of questions specific to survivors with disabilities.

**Table 1 table1:** Research questions, outcome measures, and time of data collection.

	Research question	Audience		Time and method of data collection		
		Survivor	Staff	Baseline survey	Follow-up survey	Individual interview
1	What is the initial treatment effect of SC+^a^, as compared to SC^b^, on survivors’ housing knowledge, housing self-efficacy, and staff trust?	✓		✓	✓	
2	What is the estimated sample size needed for a full intervention trial? What is the estimated timeline needed to achieve the full intervention trial sample size?	✓				
3	Are the expected rates of recruitment and retention achieved?	✓				
4	Are the study’s processes and instruments feasible for a full intervention trial?	✓		✓	✓	✓
5	Is the tool acceptable and usable by survivors and staff?	✓	✓		✓	✓

^a^SC+: standard care plus.

^b^SC: standard care only.

#### Sociodemographics

The study will collect sociodemographic information from participants at baseline. Variables include age, gender, income, length of time with the site, prior or current domestic violence exposure, housing status, and experiences of housing instability in the last 6 months.

#### Housing Knowledge

As no known prior studies have measured housing knowledge, we will assess whether the tool improves survivors’ knowledge of housing options through a 10-item Housing Knowledge Quiz developed for this study (Table 2). Questions like “Which housing program is a lottery of affordable housing apartments in New York City?” will ask survivors about affordable housing programs in New York City and program eligibility criteria, with each question carrying a 1-point weight for a possible summed score range of 0 to 10.

**Table 2 table2:** Housing knowledge quiz.

Question	Answer choices
1. Jane is a survivor of domestic violence in shelter. She and her two children plan to move out of shelter to an apartment. What is Jane’s household size?	1,2,3
2. “Affordable housing” means that you pay about one-third or less of your income on rent.	True, False
3. Eligibility for New York City housing programs can depend on your...	Household size, Income amount, Citizenship or residency status, Current living situation, Whether you have children or are expecting children, Disability, All of the above
4. Which housing program is a lottery of affordable housing apartments in New York City?	FHEPS^a^, Housing Connect, Property Management Companies, Do Not Know. Please select one answer.
5. Which housing program lists apartment openings, reviews housing applications, and takes payment?	FHEPS, Housing Connect, Property Management Companies, Do Not Know. Please select one answer.
6. Which housing program is a type of rental assistance paid directly by the government to the landlord? The amount of rental assistance will vary by one’s income and household size.	FHEPS, Housing Connect, Property Management Companies, Do Not Know. Please select one answer.
7. DHS^b^ shelter provides a time-limited stay only for households of domestic violence.	True, False
8. Supportive housing is a type of permanent housing that also includes services like case management, medical, and psychiatric help.	True, False
9. Who may be eligible for SSI^c^ benefits?	Individuals or couples who are 65 years or older, blind, or disabled, with limited income and resources, Children who are disabled or blind, with limited income and resources, All of the above, None of the above
10. What is the name of a property management company that manages affordable and low-income housing in New York City?	Reliant Realty, Insignia, Barrier Free Living, Urban Resource Institute. Please select one answer.

^a^FHEPS: family homelessness and eviction prevention supplement.

^b^DHS: Department of Homeless Services.

^c^SSI: supplemental security income.

#### Housing Self-Efficacy

According to social cognitive theory, the stronger one’s self-efficacy, the higher the goals one sets and the more favorable the outcomes one expects, and vice versa [33]. In Cattaneo and Chapman’s [28] empowerment process model, likewise, self-efficacy drives the rest of the components: power-oriented goals, knowledge, competence, action, and impact. To measure whether the tool improves survivors’ abilities to achieve their housing goals, we have constructed a 10-item Housing Self-Efficacy Likert scale (Table 3), adapted from three existing scales to incorporate housing: the Generalized Self-Efficacy Scale [34], the Financial Self-Efficacy Scale [35], and the Scale of Economic Self-Efficacy [36]. The questions have been constructed using 4 response categories, from 1=strongly disagree to 4=strongly agree. Participants will be asked to rate their level of agreement on questions such as “I can always manage to solve difficult housing problems if I try hard enough” and “If I experience housing trouble, I can usually think of a solution.” To balance the potential “forced-choice” nature of the four categories, a “does not apply” option has also been added.

**Table 3 table3:** Housing self-efficacy scale.

No.	Item
1	I can always manage to solve difficult housing problems if I try hard enough.
2	If I have a housing problem, I can find ways to get what I need.
3	It is easy for me to stick to and accomplish my housing goals.
4	I am confident that I could deal efficiently with unexpected housing events.
5	Thanks to my resourcefulness, I know how to handle unforeseen housing situations.
6	I can solve most housing problems if I invest the necessary effort.
7	I can remain calm when facing housing difficulties because I can rely on my abilities.
8	When I am confronted with a housing problem, I can usually find several solutions.
9	If I experience housing trouble, I can usually think of a solution.
10	No matter what housing problem comes my way, I am usually able to handle it.

#### Staff Trust

Trust is defined as an individual’s expectation that their needs will be met without any harm ​[37]​. When developing the tool, the coalition of housing specialists continually expressed an interest in knowing how the tool would affect survivor trust in staff. For them, they hoped the tool could validate and explain the staff’s housing advice to survivors. An abundance of research further illustrates the importance of trust in service delivery. Patient trust in health care settings, for instance, has been correlated with patient satisfaction and continuity of care [38-41]​. While several valid, reliable scales have been designed to measure trust in service delivery ​[38,42,43], no trust scale quite captures the uncertainty of the emergency shelter context or the often-volatile relationship between staff and survivors. The 10-item Trust in Community Health Workers (CHWs) Scale ​[37]​ was thus adapted to measure survivors’ perceptions of staff trustworthiness, particularly of their case managers. CHWs in low- and middle-income countries are comparable to case managers in domestic violence agencies in that both typically work with vulnerable groups in resource-constrained, emergency settings. We adapted the Trust in CHWs Scale then, not only for its validity and reliability but also for its applicability to an emergency setting, like that of a domestic violence center. Like the Housing Self-Efficacy Scale, the resulting Staff Trust Scale (Table 4) will use 4 response categories, from 1=strongly disagree to 4=strongly agree, along with a “does not apply” category for additional scenarios. Sample questions include, “My case manager tells me everything I need to know when dealing with my housing problems” and “In my opinion, my case manager is committed to providing me with the best care possible.”

**Table 4 table4:** Staff Trust Scale.

No.	Item
1	My case manager tells me everything I need to know when dealing with my housing problems.
2	My case manager knows as much as they can about finding housing.
3	My case manager takes enough time with me during our housing meetings.
4	My case manager keeps what we discuss confidential or private from others at [agency name].
5	In my opinion, my case manager is committed to providing me with the best care possible.
6	My case manager is an excellent listener.
7	I feel better emotionally after talking to my case manager.
8	My case manager treats me with respect.
9	My case manager has my best interest at heart.
10	My case manager makes me feel like I am worthy of their time.

#### Sample Size, Recruitment and Retention Rates, and Timeline

We will estimate the desired sample size for a full-scale trial based on the effect sizes achieved in this study in the housing knowledge, housing self-efficacy, and staff trust variables. Both the rates of recruitment and retention will be measured quantitatively; the recruitment rate will be defined as the number of participants who enroll divided by the total number of participants recruited, while the retention rate will be defined as the number of participants who complete the follow-up survey divided by the number of participants who complete the baseline survey. Finally, the timeline, or the time it takes to recruit participants, will be recorded to give a benchmark for the full-scale intervention trial.

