### Research Questions

Through this study protocol, we are seeking to answer the following research questions: (1) What is the initial treatment effect of SC+ (standard care plus), as compared to SC (standard care), on survivors’ housing knowledge, housing self-efficacy, and staff trust? (2) What is the estimated sample size needed for a full-scale intervention trial? What is the estimated timeline needed to reach this sample size? (3) Are the expected rates of recruitment and retention achieved? (4) Are the study’s processes and instruments feasible for a full-scale intervention trial? and (5) Is the tool acceptable and usable by survivors and staff?

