### Feasibility Criteria

As recommended by Thabane et al [44], we established formal Stop or Go criteria to evaluate the success of the feasibility study. A Stop outcome states that the subsequent large-scale trial is not feasible, while a Go outcome means that the study can continue, with or without modifications [44]. The outcomes will be determined after assessing the study data. We will stop if (1) no positive change approaching significance in any of the primary outcomes in SC+: survivors’ housing knowledge, housing self-efficacy, or staff trust, relative to SC, is observed; or (2) survivors, on average, do not intend to continue the use of the tool, as measured by scores of 2=Disagree or 1=Strongly Disagree on the Likert scale. Criteria #1 and #2 will help us determine whether SC+ shows promise of a positive effect and acceptability (as determined by intent to use) to warrant a subsequent intervention trial to a larger group. If either Stop criterion is met, then the full-scale study is not feasible.

If both Stop criteria are not met, then we can move to a Go, that is, continue to a large-scale trial. Modifications will be needed if (1) 75% or more of the questions in the survey are left unanswered, (2) 75% or more of potential survivor participants do not join the study, or (3) less than 95% of enrolled survivors do not complete both the baseline and follow-up surveys. This retention rate is informed by the retention rates of the web-based myPlan evaluation, which hovered around 94% at 6 months and 93% at 12 months [27]. The Go criteria will help us determine whether the study could enroll and engage sizable participation, as illustrated by the rates of recruitment, retention, and response. 

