## Results

Recruitment for the SC arm began in March 2022 and completed in April 2023. Of the prospective participants, 75 participants were screened, 44 participants were deemed eligible, 35 participants were enrolled (ie, consented to the study), and 23 participants completed both baseline and follow-up surveys. Initially, we had sought to attain 50 completed surveys, 25 in each arm. However, the recruitment timeline for SC took longer than anticipated, and the enrollment numbers were lower than expected. Following 1 year of recruitment for SC that resulted in 23 completed surveys, we sought to expedite the recruitment timeline for SC+. Recruitment for the SC+ arm started in January 2024 and is anticipated to end by May 2024. After SC+ arm recruitment ends, we plan to recruit, conduct, and complete the key informant interviews in June 2024. We subsequently expect to complete the study and be ready to analyze the results by the end of June 2024.

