## Discussion

### Hypothesized Findings

Among the results, we anticipate that SC+ will show a positive change relative to SC on at least one of the primary outcomes: survivors’ housing knowledge, housing self-efficacy, or staff trust. While the change may or may not be statistically significant, we are looking for the direction of change as an indication of possible future change in a large-scale trial. We also expect that most survivors in the SC+ group will deem the tool usable and acceptable. Overall, we anticipate achieving a Go outcome on feasibility for subsequent testing, likely with modifications to processes such as recruitment and retention.

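### The full-scale sample size is to be taken from effect sizes observed with about 25 completers per arm or fewer, which is too imprecise to support a fully powered next trial

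*Protocol article*

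**What the plan says.** Research question 2 asks: "What is the estimated sample size needed for a full-scale intervention trial". The answer is fixed in the subsection of Outcome Measures that deals with sample size and timeline, where the authors write: "We will estimate the desired sample size for a full-scale trial based on the effect sizes achieved in this study". The outcomes concerned are knowledge of housing, self-efficacy and trust in staff. The protocol names no smallest difference worth detecting, no allowance for imprecision, and no rule for choosing among the three effects.

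On study size, the Results section says: "Initially, we had sought to attain 50 completed surveys, 25 in each arm". In SC, "23 participants completed both baseline and follow-up surveys", out of 35 enrolled, after about a year of recruitment. For the tool arm, SC+, the window was shortened ("we sought to expedite the recruitment timeline for SC"+) to January to May 2024, and no achieved or revised number is given.

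Two passages bear on which observed effects lead to a next trial. Feasibility Criteria stops the programme if there is "no positive change approaching significance in any of the primary outcomes in SC"+ relative to SC, without defining near-significance. Hypothesized Findings is looser: the change need not be significant, and "we are looking for the direction of change". The section This Study describes next-phase trials as having full power to measure impact.

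**The concern.** The required sample size varies with the inverse square of the effect, so a modest error in the effect becomes a large error in N. An effect estimated from about 25 per arm has a standard error of the same order as the effects one would hope to see. A trial sized on it may have far less, or far more, power than it claims. A near-significance condition adds selection: if only large observed effects lead to a next trial, the effects used to size it tend to be too large.

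At stake is the answer to research question 2. An undersized next trial would burden survivors and a stretched site, and could dismiss a useful tool.

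**Working it through.** **Inputs from the protocol.** Target 25 completers per arm; 23 SC completers of 35 enrolled; three outcomes analysed by difference-in-difference regression.

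**Assumptions, because the protocol gives no figure.** SC+ completers 25 (the original target) or 15; effects in SD units of change; next trial with two-sided 5% and 80% power; near-significance read as two-sided p<0.10 or p<0.20; correlation between outcomes from 0 to 0.6.

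**The plan's own figure.** There is none to reproduce. The target of 25 per arm comes without effect, SD, alpha or power, and no full-scale N is stated.

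**Step 1: precision.** SE(d) ≈ √(1/n₁ + 1/n₂).
- 23 vs 25: √(0.0435 + 0.0400) = 0.289; 95% half-width 1.96 × 0.289 = 0.57.
- 23 vs 15: √(0.0435 + 0.0667) = 0.332; half-width 0.65.

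**Step 2: what this does to N.** N per arm = 2(1.96 + 0.8416)²/d² = 15.70/d², rounded up. A true d of 0.4 needs 15.70/0.16, that is 99. The middle half of estimates is 0.4 ± 0.6745 × SE; the chance of an estimate at or below zero is Φ(−0.4/SE).

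| Completers | Middle half of observed d | N per arm implied | Estimate zero or negative |
|---|---|---|---|
| 23 vs 25 | 0.205 to 0.595 | 374 down to 45 | 8% |
| 23 vs 15 | 0.176 to 0.624 | 506 down to 41 | 11% |

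Half of all repetitions fall outside even these ranges.

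**Step 3: the condition for continuing, read strictly.** With 23 vs 25, p<0.10 needs an observed d of about 0.485, so one passing outcome cannot imply more than 15.70/0.485² = 67 per arm. p<0.20 needs about 0.376, so at most 112. A true d of 0.3 needs 15.70/0.09, that is 175, so every passing outcome undersizes the trial at either threshold.

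Simulating three outcomes with true d = 0.3, 23 vs 25 and continuation at p<0.10 gives:

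| Effect used for sizing | Median N per arm | Repetitions with N below 175 |
|---|---|---|
| Largest of three | about 37 | all |
| Mean of three | about 67 to 107 | 74 to 92% |
| Smallest of three | above 175 at low correlation, below it at 0.6 | 19 to 56% |

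Ranges cover the assumed correlations. True power at d = 0.3 is Φ(0.3√(N/2) − 1.96): 25% at 37 per arm, 41% at 67 and 59% at 107.

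**Step 4: the looser reading.** If only the direction must be favourable, sizing on the mean effect is too small in about half of repetitions, so there is little systematic bias. Sizing on the largest is too small in about 82% (correlation 0.3), because picking the largest of three selects by itself.

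**The case against.** A reader might infer that the projected sample size will be systematically too small. The document does not support that without conditions. It does not say which of the three effects will be used: a team wanting power on every outcome would take the smallest, and the error would then often run toward too large an N or none at all. It does not define near-significance, and Hypothesized Findings speaks only of direction. If the true effect is large (0.8 SD or more), the condition removes few studies and adds little bias. All of this stands and limits the point on bias. None of it touches the imprecision in Steps 1 and 2, which is present whatever the condition.

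A reader might also prorate SC's recruitment pace and assume a very small SC+ arm. No SC+ count is given, and SC's pace was reduced when about half its participants were found ineligible midway (Considerations), so prorating could mislead. Hence the stated range of 15 to 25.

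Finally, the protocol asks only for an estimate, nothing in the present study's conduct depends on it, and basing N on observed effects does not rule out showing an interval. That keeps the matter from being critical. But an interval alone would not rescue the method: at 23 vs 25, any observed d below about 0.57 has a lower limit below zero, where no N exists.

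**Conclusion.** The point holds as one of imprecision. The rule is written in the protocol and is not a detail left to an analysis plan. Followed as stated, it gives an unreliable answer to research question 2: for an assumed true effect of 0.4 SD, a correct 99 per arm could readily come out as 45 or 374 (23 vs 25), or 41 or 506 (23 vs 15), with no usable figure in 8 to 11% of cases.

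Downward bias is a conditional addition. It is strong when near-significance is enforced and the passing or largest effect is carried forward, and clear for the mean. It is small under the direction-only reading with the mean effect, and can reverse if the smallest effect is used.

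SC+ size, true effect, thresholds, correlation, alpha and power are all assumptions. Any bias in the observed effect from the sequential, non-randomised comparison would come on top and is not counted here. The change should be made, but the feasibility study itself is not invalidated.

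**What to change.** Replace the sizing rule with a short paragraph stating that:

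- the full-scale N will rest on a prespecified smallest worthwhile difference for each outcome (for example, in quiz points), agreed with the site;
- this study supplies only the SD of change, the baseline/follow-up correlation and retention. Using the upper 80% confidence limit of the SD instead of the estimate multiplies N by about 1.21 at 48 degrees of freedom;
- N will be shown over a grid of differences. For 0.2, 0.3, 0.5 and 0.8 SD it is 393, 175, 63 and 25 completers per arm. At the SC completion of 23/35, 175 becomes 175 × 35/23, that is 267 enrolled per arm, and 63 becomes 96;
- observed effects will be reported with confidence intervals, as context only.

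The cost is more than drafting. The quiz was developed for this study and the two scales are adaptations, so the documents offer no ready anchor for a worthwhile difference and it has to be discussed with the site. The grid keeps the answer usable if agreement is incomplete. The projected N will usually be larger than under the current rule. No new data are needed.

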### Future Directions

#### Considerations

When implementing the SC arm, the study team encountered several delays with data collection that have been highlighted here for future consideration.

To start with, the study was conducted during the pandemic, at a time when nonprofits, like the partner site, were experiencing significant labor shortages and funding constraints [49,50]. At the same time, demand for services continued to increase, leading more nonprofits to report a decrease in their ability to provide services [51]. As such, the study’s data collection efforts often inadvertently competed with the staff’s full workload. In turn, the crisis context of domestic violence work also may have prevented the staff from fully participating in the study as they had hoped.

Further delaying data collection were unanticipated enrollment issues. Halfway through SC recruitment, we discovered about half of the SC participants were not truly eligible for the study. We infer that some participants had forwarded the study information to friends and family, who then falsely answered the screening questions to participate in the study. While we subsequently removed those faulty participants, we also extended the SC recruitment timeline to make up for the loss.

Finally, the study team had not accounted for the time it would take to obtain the appropriate site approvals, nor had we prepared for an unexpected change in case management systems.

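### Elapsed recruitment time is not a valid benchmark for the full-scale timeline: the team shortened the SC+ window, SC closed short of target, and no participants-per-month rate is defined

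*Protocol article*

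**What the plan says.** The second half of research question 2 asks: "What is the estimated timeline needed to reach this sample size". The measure meant to answer it, in Sample Size, Recruitment and Retention Rates, and Timeline, is duration: "the timeline, or the time it takes to recruit participants, will be recorded to give a benchmark for the full-scale intervention trial". Statistical Analysis adds only that the timeline will be recorded along with the other feasibility measures.

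The one quantity called a rate of recruitment has no time in it: "the recruitment rate will be defined as the number of participants who enroll divided by the total number of participants recruited".

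On how the two arms were run:

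- **Target** (Results): "Initially, we had sought to attain 50 completed surveys, 25 in each arm".
- **SC** (Results): "Recruitment for the SC arm began in March 2022 and completed in April 2023". It yielded 75 screened, 44 eligible, 35 enrolled and 23 completers. The same section also describes this period as one year.
- **SC extension** (Considerations): about half of the SC participants were found, midway, not to be truly eligible. They were removed, and "we also extended the SC recruitment timeline to make up for the loss".
- **SC+** (Results): "Recruitment for the SC+ arm started in January 2024 and is anticipated to end by May 2024". The Abstract attributes the faster schedule to slow SC recruitment and limited overall study time. Recommendations says that the SC+ recruitment period was shortened. No new target for SC+ is given.

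**The concern.** The time taken to recruit tells the planner of the next trial something only if the number recruited was fixed and the time was left free. In SC+ it is nearer the reverse: the team set the window, and the number enrolled is what will be observed. In SC neither was cleanly fixed, since the arm was extended to replace removed participants and then closed two short of its target. Recording the two durations as the benchmark would hand the next trial a figure that is partly the team's own decision.

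The stated primary objective is to judge whether a full-scale trial is feasible, and slow accrual was the main difficulty in SC. A timeline that does not reflect accrual speed could lead to a wrong recruitment period or a wrong number of sites.

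**Working it through.** **1. Inputs.** From Results: 23 SC completers; SC open March 2022 to April 2023; SC+ open January to an anticipated May 2024; original target 25 per arm. Only months are given. The SC window is therefore taken as 12 to 14 months (one year at the short end, both months counted in full at the long end) and the SC+ window as 4 to 5 months. The target of 25 has no stated effect size, SD, alpha or power, so there is no plan figure to reproduce.

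**2. SC accrual.** Rate = completers / months open, with an exact Poisson 95% interval: lower limit χ²(0.025; 46)/2 and upper limit χ²(0.975; 48)/2, each divided by months.

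| Months open | Completers per month | 95% interval |
|---|---|---|
| 12 | 23/12 = 1.92 | 1.22 to 2.88 |
| 13 | 23/13 = 1.77 | 1.12 to 2.65 |
| 14 | 23/14 = 1.64 | 1.04 to 2.47 |

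**3. What the SC+ window would yield at the SC rate.** 1.64 × 4 = 6.6 and 1.92 × 5 = 9.6, so about 7 to 10 completers.

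**4. What the SC+ duration alone says.** Assume a full-scale total of 126, which is 63 per arm for a standardised difference of 0.5 at two-sided alpha 0.05 and 80% power. The protocol gives no such figure. The same 4 to 5 month window is compatible with very different projections, 126 / (count / months):

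| SC+ completers (assumed) | Per month | Months to reach 126 |
|---|---|---|
| 4 | 0.8 to 1.0 | 126 to 158 |
| 8 | 1.6 to 2.0 | 63 to 79 |
| 15 | 3.0 to 3.75 | 34 to 42 |
| 25 | 5.0 to 6.25 | 20 to 25 |

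One recorded duration thus fits answers from 20 to 158 months. Only the count separates them.

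**5. What a rate gives.** Timeline = required number / rate. At 1.64 to 1.92 per month and one such site, assumed totals of 50, 126 and 350 (standardised differences 0.8, 0.5 and 0.3, same alpha and power) take about 26 to 30, 66 to 77 and 183 to 213 months. Carrying the Poisson limits through for 126 gives 126/2.88 = 44 to 126/1.04 = 121 months, so the projection is usable but imprecise.

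**6. The SC extension.** Its length is not stated. If 2, 4 or 6 of 14 months were extension (assumed) and were dropped while all 23 completers were kept, the rate would move from 1.64 to 23/12 = 1.92, 23/10 = 2.30 or 23/8 = 2.88. The whole window belongs in the denominator, with the removed participants excluded from the count. The article says that they were removed but not whether 75, 44 and 35 exclude them.

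**The case against.** The strongest reply is that nothing is lost. Counts and dates are both recorded, SC counts are already published with start and end months, and anyone can divide one by the other. A fixed window with a known count estimates accrual as well as a fixed count with a known time. The shortening and the extension are openly disclosed, no Stop criterion or modification trigger uses the timeline, and the conversion to a projection could sit in a fuller document. Most of this stands. It shows that the data suffice and that no Stop or Go decision is at risk. It does not rescue the stated measure, because the article names duration as the benchmark and does not say that a rate will be formed.

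Three stronger readings are tempting but not supported:

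- **Research question 2 cannot be answered.** Only its timeline half is touched, and a rate can be derived for it.
- **The benchmark will understate the time needed, perhaps about threefold.** That requires reading the SC+ window as the time to fill 25 places (5.0 to 6.25 per month, 2.6 to 3.8 times the SC rate). No section reads it so, and the 25 per arm is described as the initial aim. The article does not say which arm supplies the benchmark. SC elapsed time may err the other way, since it includes the extension, and Considerations also lists pandemic staffing, approvals and a system change among the delays.
- **The SC extension spoils SC, or SC+ closes on a fixed date.** Genuine completers over the full SC window remain a valid rate. May 2024 is an anticipated end; the documents establish that the team shortened the window, not that a closing rule exists.

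**Conclusion.** The point holds for the timeline half of research question 2. As written, the benchmark is a duration that for SC+ was set partly by the team, and that for SC is not a time to target because the arm was extended and ended at 23 of 25. The direction of any resulting error is unknown.

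The reference figure is the SC rate of 1.6 to 1.9 completers per month. It assumes that the 23 completers are all genuine, that recruitment was open throughout the stated months, and that SC conditions are representative; the last is doubtful given the delays reported. The projections in months also rest on assumed full-scale totals and a single site. The weakness is worth correcting before the results are written up, but it does not threaten the study's Stop or Go decision.

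**What to change.** Replace elapsed time as the benchmark with two rates, reported separately for SC and SC+: confirmed-eligible enrolled participants, and completers, per month of open recruitment, each with an exact Poisson 95% interval. Derive the full-scale timeline as the required number divided by the rate, carrying the interval through.

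Alongside this:

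- State that the team set the SC+ duration, so it is not itself a finding.
- Use the whole SC window as the denominator, exclude removed participants from the counts, and say whether 75, 44 and 35 already do so.
- Give the length of the SC extension and any period when recruitment was paused.
- Give exact opening and closing dates and reconcile the one-year description with March 2022 to April 2023. Moving from 12 to 14 months changes the rate from 1.92 to 1.64.

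The cost is a few sentences and a short calculation from dates and counts already held. The drawback is a wide interval, given 23 completers in SC and possibly fewer in SC+, and probably a less favourable projected timeline.
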